## Abstract

**Background:**

Lipoprotein-associated phospholipase A_2_ (Lp-PLA_2_), a biomarker of oxidation and inflammation, has been associated with increased coronary artery disease risk. To date, very few studies have examined the Chinese herbal drug Danshen or its extract on Lp-PLA_2_ in patients with stable angina pectoris. In this study, we aim to investigate the effect of Danshen extract on Lp-PLA_2_ level in patients with stable angina.

**Methods/design:**

This is a randomized, single-blind, placebo-controlled, adaptive clinical trial. A total of 156 patients meeting the eligibility criteria will be randomly assigned to either the Danshen extract (DanshenDuofensuanyan injection and Danshen drop spill) group or the placebo group in a 1:1 ratio. Participants will then undergo treatment with DanshenDuofensuanyan injection or placebo (glucose) during hospitalization, followed by open-label Danshen drop spill (30 pills/day) in Danshen extract group for 60 days after discharge. Because this is an adaptive trial, two interim analyses are prospectively planned. These will be performed after one-third and two-thirds of the patients, respectively, have completed the trial. On the basis of the results of these interim analyses, a data monitoring committee will determine how to modify aspects of the study without undermining the validity and integrity of the trial. The primary outcome measure is the serum level of Lp-PLA_2_ in the Danshen extract group and the placebo group. The secondary outcomes include the proportion of patients who show a clinically significant change, which is defined as at least a 20-point improvement in angina frequency score on the Seattle Angina Questionnaire and the carotid intima-media thickness, which will be measured using ultrasound. Other secondary efficacy and safety outcomes will also be assessed.

**Discussion:**

This study will provide evidence that Danshen extract is beneficial for stable angina and may establish a possible mechanism of Danshen treatment effects on cardiovascular disease. This study may also validate an objective blood test (LP-PLA_2_ level) for assessing the effectiveness of Danshen therapy in patients with stable angina pectoris.

**Trial registration:**

ClinicalTrials.gov, NCT02870764. Registered on 13 August 2016.

**Electronic supplementary material:**

The online version of this article (doi:10.1186/s13063-017-2336-2) contains supplementary material, which is available to authorized users.

## Background

Cardiovascular disease is the leading cause of death worldwide, accounting for 17.3 million deaths per year, and is predicted to reach 23.6 million annually by 2030 [1]. Chronic stable angina makes up 50% of all patients with coronary artery disease (CAD) [2]. Its symptoms are highly related to the development of atherosclerotic plaque that obstructs at least one large epicardial coronary artery and triggers an imbalance between myocardial oxygen supply and demand.

Inflammation has been found to play critical and continuous roles on the initiation and progression of atherosclerosis and CAD [3, 4]. Of all the key inflammation biomarkers, lipoprotein-associated phospholipase A_2_ (Lp-PLA_2_) is an enzyme secreted predominantly from atherosclerotic plaques by macrophages and neutrophils and then circulates in the bloodstream [5]. This offers several advantages relative to other inflammatory markers, including specificity for vascular inflammation, minimal biovariability, and stability in cases of myocardial ischemia. Several studies have demonstrated that Lp-PLA_2_ is strongly expressed in macrophages in the fibrous cap of coronary lesions prone to rupture as well as within the necrotic core [6, 7]. Furthermore, the intensity of Lp-PLA_2_ staining is closely related to plaque vulnerability [7]. In a prospective cohort study of patients undergoing carotid endarterectomy, Lp-PLA_2_ expression was higher in plaques from patients with CAD than in plaques from those without CAD [8]. In addition, Lp-PLA_2_ mass was demonstrated to predict future cardiovascular events in patients with stable CAD [9–12]. In a majority of studies, Lp-PLA_2_ has been shown to be an independent predictor of future events, even after adjustment for several conventional risk factors. All these findings strongly suggest that decreasing the Lp-PLA_2_ level in patients with CAD may improve their clinical outcomes and that the serum Lp-PLA_2_ level may be used as a marker for the effectiveness of treatments for CAD.

Given Lp-PLA_2_’s role as a key modulator of oxidative stress, inflammation, and atherosclerosis [13] and that it overlaps with the effects of Danshen therapy [14], Danshen likely works through lowering Lp-PLA_2_ levels to achieve its efficacy in inhibiting oxidative stress and inflammation. Danshen, the dried root of *Salvia miltiorrhiza*, is one of the most versatile Chinese herbal drugs. Danshen can improve microcirculation, vasodilate coronary vessels, suppress inflammation, and protect against myocardial ischemia [14–16]. It is widely used either alone or in combination with other herbal ingredients for patients with CAD and other cardiovascular diseases in China and, to a lesser extent, in other countries, including the United States.

Authors of two previous systematic reviews concluded that Danshen extract added to conventional therapy in patients with CAD reduced major adverse cardiac events and improved patient survival [17, 18]. However, the mechanisms behind these findings have not been studied before. We hypothesized that Danshen treatment acts on Lp-PLA_2_ to beneficially affect patients’ clinical outcomes. Thus, the aim of our present trial is to investigate the effect of Danshen extract on serum Lp-PLA_2_ levels in patients with stable angina.

## Methods/design

### Design

The Effect of Dan-shen Extract on Lipoprotein-associated PHospholipase A2 Levels in Patients with Stable Angina Pectoris study (DOLPHIN study) is a prospective, randomized, single-blind, placebo-controlled study designed to evaluate the effect of Danshen extract (DanshenDuofensuanyan, also known as *salvianolate*) and Danshen drop pills, with both these two drugs having as their main active ingredient Danshen extract (*Salvia miltiorrhiza*), on Lp-PLA_2_ levels in patients with stable angina. The trial is registered with ClinicalTrials.gov (NCT02870764), and the full trial protocol can be accessed at https://clinicaltrials.gov/ct2/show/NCT02870764?term=dolphin&rank=4.

### Patients

The DOLPHIN study will be performed in Taizhou Fourth People’s Hospital, Taizhou, China. Patients with stable angina will be recruited. The study flowchart is shown in Fig. 1, and detailed inclusion and exclusion criteria are listed in Table 1. The detailed study schedule is provided in Fig. 2, and the Standard Protocol Items: Recommendations for Interventional Trials (SPIRIT) checklist [19] is provided in Additional file 1.

**Fig. 1 Fig1:**
[figure not shown]
Flowchart of the trial

**Table 1 Tab1:** Inclusion and exclusion criteria

Inclusion criteria	Exclusion criteria
1. Aged 18–75 years 2. Written informed consent provided 3. Patients with a clinical diagnosis of chronic stable angina who fulfill one of the following conditions: a. Symptoms that support the diagnosis of chronic angina, and/or a history of an abnormal exercise response limited by angina, and/or electrocardiographic changes b. A history of myocardial infarction and ST-T changes c. Stenosis greater than 50% in at least one major epicardial coronary artery, as shown by coronary angiography or computed tomographic angiography d. Coronary heart disease confirmed by radionuclide angiocardiography 4. Patients with moderate angina pectoris, which is defined as grade II or III on the Canadian Cardiovascular Society Angina Grading Scale	1. Patients with severe complications that would complicate the condition, as assessed by the investigator, including liver or renal dysfunction, severe cardiopulmonary dysfunction, pulmonary hypertension, chronic obstructive pulmonary disease, a history of epilepsy, or cerebral hemorrhage 2. Patients who experienced myocardial infarction or who were classified as grade IV on the Canadian Cardiovascular Society Angina Grading Scale within the preceding 3 months 3. Patients with chest pain that is caused by any other disease (e.g., acute myocardial infarction, severe neurosis, menopausal syndrome, or hyperthyroidism) 4. Patients with a history of drug-induced bleeding or a history of bleeding caused by warfarin 5. Patients with a history of hematopoietic disorder 6. Patients who have had surgery within the previous 4 weeks or who have a hemorrhagic tendency 7. Women who are pregnant or lactating or who have a positive pregnancy test, or women who have a menstrual period at baseline 8. Patients who are participating in other trials or who have participated in other trials within the past 3 months 9. Patients with a history of allergy or with a known or suspected allergy to the study drug 10. Patients with a known or suspected history of alcohol or drug abuse within the past 2 years 11. Patients with a mental disorder 12. Family members or relatives of the study center staff 13. Inability to adhere to study procedures

**Fig. 2 Fig2:**
[figure not shown]
The schedule of enrollment, interventions, and assessments. *Blood RT* Blood routine test, *Echo* Echocardiography, *EKG* Electrocardiography, *IMT* Carotid intima-media thickness, *Lp-PLA*
_*2*_ Lipoprotein-associated phospholipase A_2_

### Randomization and blinding

Randomization will be carried out by an independent randomization coordinator from Taizhou Fourth People’s Hospital according to a 1:1 intervention-to-control ratio. The physicians, patients, evaluators, and statistician will be blinded to which treatment group the participant has been allocated, except for nurses who will deliver the drugs, and the nurses who deliver the drugs will be blinded to the physicians, evaluators, and statistician and will not participate in the data collection or analysis.

Participants and relevant researchers will be blinded to DanshenDuofensuanyan (salvianolate) injection therapy or placebo treatment group assignments during the whole study period. Because the color of DanshenDuofensuanyan injection and 5% glucose injection are different, the dropping bottles will be wrapped in sealed, shaded bags during infusion, and brown infusion devices will be used for infusion. The nurses will check and verify the integrity of wrapping throughout the infusion.

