### Treatment

According to the Chinese guidelines for the diagnosis and treatment of chronic stable angina [24], participants included in this trial will receive the standard conventional therapy as a basic treatment, including oral nitrates, statins, β-blockers, and antiplatelet agents, in addition to the Danshen extract treatment or placebo treatment. Because statins can have an effect of reducing Lp-PLA_2_ levels in a dose-dependent manner, all participants will receive atorvastatin 20 mg per night. If the patients are not suitable for receiving atorvastatin therapy, another isodose statin will be used. All treatments will be recorded in detail in the patients’ medical records as well as in their case report forms (CRFs).

Participants in the Danshen extract group will be treated using DanshenDuofensuanyan (200 mg per day) plus 0.9% saline injection (250 ml intravenously per day), whereas participants in the placebo group will be treated using placebo (glucose 200 mg per day) plus 0.9% saline injection (250 ml intravenously per day). If the patient has diabetes mellitus, glucose will be balanced with insulin. All of the included patients will undergo a 70-day treatment regimen during which patients in the Danshen extract group will receive a 10-day of course DanshenDuofensuanyan therapy in a double-blind manner and then continue to receive Danshen drop pills (a Danshen extract formulated for oral administration) unblinded, whereas the patients in the control group will receive standard medical care only. Study drugs will be provided by Shanghai Green Valley Pharmaceutical Co., Ltd. (Shanghai, China); however, they will not be involved in the design, patient recruitment, treatment, data collection and analysis, or any other procedures that would bias the study results.

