#### Secondary objectives

The secondary outcomes are as follows:The proportion of patients in each treatment group who have clinically significant changes as defined by the angina frequency score on the Seattle Angina QuestionnaireCarotid arterial intima-media wall thicknessThe frequency of angina attacks per weekAngina grade according to the Canadian Cardiovascular Society Angina Grading ScaleConsumption of short-acting nitratesChanges in electrocardiogram resultsChanges in serum lipid levels, high-sensitivity C-reactive protein levels, and the rate of platelet aggregation

These outcomes will be assessed at the same time points as the primary outcome. The safety of Danshen extract therapy will be evaluated by the incidence of new-onset major vascular events, overall mortality, and incidence of severe and moderate hemorrhages during patients’ hospitalization and 60 days after discharge. After each interim analysis, the DMC will determine whether the study can continue or there is a need to modify or terminate the study.

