## Discussion

Danshen, also known as *Salvia Militorrhizashen*, is considered one of the most important traditional Chinese medicines and has been widely used in Asian countries. It has been used for hundreds of years in the treatment of numerous ailments, including cardiovascular disease [14]. According to Chinese medicine theory, Danshen promotes blood flow and resolves blood stasis [25]. Although Danshen or its ingredients, including DanshenDuofensuanyan (salvianolate) and Danshen drop pills used in this study, improve the outcomes of patients with cardiovascular disease [26, 27], the mechanism of action remains unclear [28–30]. Inflammation plays an important role in the etiology of atherosclerosis and CAD [31]. We thus hypothesized that Danshen may improve the clinical outcomes of patients with CAD through its anti-inflammatory effect.

Lp-PLA_2_ belongs to the superfamily of PLA_2_ enzymes which are produced by macrophages that appear to play a role in the atherosclerotic vessel wall. Lp-PLA_2_ can be identified in the circulation and in atherosclerotic plaque and could act as an inflammatory marker with potential use as a predictor of cardiovascular risk and as a therapeutic target [32]. Emerging data suggest Lp-PLA_2_ is an independent predictor of risk [22] and may be superior to other inflammatory markers owing to its unique effects on the initiation and progression of atherosclerosis [33, 34] and minimal biovariation.

To our knowledge, our present study is the first double-blind, randomized trial to assess the effect of Danshen therapy on Lp-PLA_2_ level in patients with stable angina pectoris. The correlation between changing of Lp-PLA_2_ level and improvement of patient symptoms using other assessment tools, including the Seattle Angina Questionnaire, frequency of angina attacks, angina grade, consumption of short-acting nitrates, and so forth, will also be analyzed. It is well documented that a randomized controlled trial is the gold standard for evaluating the clinical efficacy and safety of a Chinese medicine and for providing critical evidence to develop and guide treatment strategies. Our results may elucidate the possible mechanism behind Danshen treatment effects in patients with cardiovascular disease and also may validate an objective blood test (LP-PLA_2_ level) for assessing the effectiveness of Danshen therapy in patients with stable angina pectoris.

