However, our study still has limitations. First, because DanshenDuofensuanyan injection will be used only during patients’ hospitalization for 10 days and Danshen drop pills will be used during the 60 days after discharge, we cannot use blind the patients after discharge, given the need for Danshen drop pill prescription. Second, statins have been proven to decrease the LP-PLA_2_ level in previous studies. As such, although a placebo control will be applied in our study, we can assess only the complementary effect of Danshen, because statins are a standard of care treatment for patients with stable angina pectoris. Finally, given budget limitations, the follow-up time is not long enough to determine whether the change of Lp-PLA_2_ level can improve patients’ long-term cardiovascular outcomes.

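### Blinding is claimed for the whole study and the trial is called double-blind without limit, but for 60 of the 70 days only the Danshen arm takes pills, openly and with no placebo

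*Protocol article*

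**What the plan says.** The article's statements on blinding fall into two groups.

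**Statements with no limit to a phase**
- Randomization and blinding, on duration: "Participants and relevant researchers will be blinded to DanshenDuofensuanyan (salvianolate) injection therapy or placebo treatment group assignments during the whole study period".
- The same section, on roles: "The physicians, patients, evaluators, and statistician will be blinded to which treatment group the participant has been allocated". The only stated exception is the nurses who deliver the drugs.
- Design: the trial "is a prospective, randomized, single-blind, placebo-controlled study". The abstract uses the same two labels.
- Discussion: "our present study is the first double-blind, randomized trial".

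**Statements that describe an open phase**
- Treatment: after the infusion course, patients in the Danshen arm "then continue to receive Danshen drop pills (a Danshen extract formulated for oral administration) unblinded".
- The same sentence, from its last word about that arm to the control arm: "unblinded, whereas the patients in the control group will receive standard medical care only".
- The abstract's methods paragraph also calls the pills open-label and gives them 60 days after discharge, in the Danshen arm only.
- Discussion, first limitation: "we cannot use blind the patients after discharge, given the need for Danshen drop pill prescription".

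On timing, the Primary objective places Lp-PLA2 measurement at inclusion, at discharge after 10 days of treatment, and 60 days after discharge. For the secondary outcomes, "These outcomes will be assessed at the same time points as the primary outcome".

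**The concern.** The two groups of statements cannot both be true after discharge. The trial is credited with masking and placebo control over its full length, and it has them only for the infusion phase.

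This matters most for symptoms at day 70. By then one group has knowingly taken an active product for 60 days and the other has knowingly taken nothing extra. Angina counts, questionnaire answers and tablet use can shift with that knowledge. If the results are read under a double-blind, placebo-controlled label, a difference caused by expectation could be credited to the drug.

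A second aim is also affected. The Discussion plans to correlate the change in Lp-PLA2 with symptom improvement, and hopes in this way to support the blood test as a measure of whether Danshen works. If knowledge of the arm moves the day-70 symptom reports, it moves that correlation too.

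**Working it through.** No stated figure needs to be reproduced. The check compares the blinding statements with the treatment and assessment schedule.

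**1. Length of the open phase.** Inputs from Treatment and the abstract: a 70-day regimen, a 10-day blinded infusion course, and 60 days of pills after discharge.
- Open days = 70 − 10 = 60.
- Share = 60 / 70 = 0.857, or 86%.

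**2. Can the whole-period claim be saved by a narrow reading?** It speaks of the injection assignment, so one could argue that open pills leave that assignment hidden. They do not. Pills follow the Danshen injection and never follow the placebo injection, so pill status and injection status are the same information. A patient who openly takes Danshen pills can infer the earlier injection. A control patient who knows the design can infer the reverse.

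**3. Which masking measures cover which phase?** The measures described under Randomization and blinding are wrapped bottles, brown infusion devices and checks of the wrapping. All concern the infusion. The article describes none for the 60 days of pills.

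**4. What is measured in the open phase?** There are two post-baseline assessments, discharge (day 10) and day 60 after discharge (day 70). The second falls at the end of the open phase. The seven listed secondary outcomes divide as follows.

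| Secondary outcome | Depends on patient report or behaviour |
|---|---|
| Seattle Angina Questionnaire responder status | yes |
| Carotid intima-media thickness | no |
| Weekly angina attacks | yes |
| Canadian Cardiovascular Society grade | yes |
| Short-acting nitrate use | yes |
| Electrocardiogram changes | no |
| Lipids, high-sensitivity C-reactive protein, platelet aggregation | no |

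The count is 4 of 7. For nitrates, the Treatment section has patients record their own nitroglycerin use.

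**5. How are the two time points analysed?** Statistical methods compares the arms on measurement data by repeated-measures analysis over baseline, day 10 and day 70. It does not distinguish the masked from the open assessment.

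**6. Who is unblinded after discharge?** The limitation in the Discussion gives up blinding for patients. It is silent on physicians, evaluators and the statistician, whom Randomization and blinding lists as blinded. Their status at day 70 is therefore claimed, but no post-discharge measure is described to support it.

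**The case against.** The strongest reply is that nothing is hidden. The abstract, the Treatment section and the first limitation all say that the pill phase is open. That stands. A reader might infer that the article passes off open-label results as blinded, but the documents do not support this: no sentence labels the day-70 symptom results as blinded. The defect is a set of unreconciled statements. Disclosure does not cure it, because the limitation covers patients only and leaves the whole-period claim and the double-blind label in place.

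Other stronger readings also fail.
- A reader might count the Treatment section among the overstatements because it uses the term double-blind. It applies the term only to the 10-day infusion, which is correct.
- A reader might infer that evaluators and the statistician can see the arm, because treatments are entered in the case report forms and these hold all results. The article does not say who can read which pages, and it defers data handling to a data management plan that is not shown. Unmasking of these roles is possible but not shown.
- A reader might conclude that discharge must become the confirmatory time point for symptoms. The article names no confirmatory time point for them. The change would rest weekly attacks and nitrate use on about 10 inpatient days and leave the oral phase out of the comparison. It is a debatable trade-off and not a correction.

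It is also fair to say that the primary outcome is a laboratory value and less exposed to expectation. The bias argument is therefore limited to the symptom outcomes and to any correlation that uses them.

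**Conclusion.** Wrong as written. The claim of blinding for the whole study period and the unlimited double-blind label contradict the article's own account of treatment after discharge. The placebo-controlled label in the abstract and the Design section holds only for the infusion phase.

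**Size.** The contradiction covers 60 of 70 treatment days (86%), one of the two post-baseline assessments, and four of the seven listed secondary outcomes at that assessment. The amount of bias cannot be derived from the document. A shift in favour of Danshen is a plausible risk and not an established fact.

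**Assumptions.** Patients in the pill arm know what they are taking, which follows from the pills being open. Control patients are assumed to know enough of the design to understand what receiving no pills means. The conclusion does not require that evaluators, laboratory staff or the statistician are unmasked.

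**What to change.** 1. Reconcile the abstract, Design, Randomization and blinding, and both Discussion statements. Use one description throughout: blinded and placebo-controlled to discharge, then open-label Danshen pills versus standard care to day 70.
2. Delete the phrase that extends blinding over the whole study period, and remove or limit to the infusion phase the double-blind label in the Discussion.
3. Report and interpret the day-70 results for questionnaire response, weekly attacks, angina grade and nitrate use as open-label, separately from the masked discharge results. Treat any correlation of Lp-PLA2 change with day-70 symptoms in the same way.
4. State whether evaluators and the readers of Lp-PLA2 samples, carotid images and electrocardiograms remain masked at day 70, and by what means, for example coded samples and images.

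Items 1 and 2 are wording. Item 3 changes presentation and adds no data collection. Item 4 is a statement if masking is already in place, or some coding work if it is not. No treatment changes. The real cost is that the day-70 symptom results will support weaker claims.
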